## Abstract

Obesity is currently becoming a serious global public health problem due to its high prevalence and continuous increase. This condition is associated with different physical and mental health problems. The presence of emotional disorders (anxiety, depression and related disorders) among candidates for bariatric surgery is very high and predicts worse physical and psychological results. The present study aims to explore the feasibility and clinical usefulness of the Unified Protocol, a transdiagnostic emotion regulation-based intervention, delivered in an online group format to patients with emotional disorder diagnosis or symptoms, who are waiting for bariatric surgery. We will conduct a pilot study with a repeated single-case experimental design (multiple baseline design) in a public mental health service. The sample will consist of 60 participants, who will be randomized to three baseline conditions: 8, 12 or 15 evaluation days before the intervention. Diagnostic criteria, symptomatology and body mass index are the primary outcome measures, and we will include affectivity, personality, quality of life, body image, eating behavior and surgical complications like secondary measures. An analysis of treatment satisfaction will be also performed. Assessment points will include pre-treatment, baseline, treatment, post-treatment, and follow-ups every three months until two years after post-treatment. The results obtained in this study may have important clinical, social and economic implications for public mental health.

## 1. Introduction

Obesity is a chronic disease characterised by an increase in body fatness, which is usually estimated by body mass index (BMI) calculated as measured body weight (kg) divided by measured height squared (m^2^) [1]. Obesity is currently becoming a serious global public health problem due to its high prevalence and increase in recent years [2]. In Spain alone, 25% of the population is obese or overweight, and the expectations are alarming. It is expected that in 2030, up to 80% of Spanish men and 55% of women will be obese or overweight, exceeding 27.2 million of people [3].

The causes of obesity are complex and multifactorial [1], and this condition is associated with different health problems, such as myocardial infarction, hypertension, stroke, dyslipidemia, diabetes mellitus, or obstructive sleep apnea [4,5,6]. All these alterations affect the quality of life and can disturb important areas of functioning (e.g., physical function, vitality, social functioning and emotional role) [7,8]. In addition to all of these complications, people with obesity experience significant psychological difficulties [7]. Due to all of these health implications, obesity represents a challenge to the countries’ economies [9]. As of 2016 in Spain, the obesity cost meant almost two billion euros of extra expenses for the National Health System [3].

For all these reasons (high prevalence and associated costs), many efforts have been made to find treatments for obesity and weight loss, which include lifestyle interventions, pharmacological interventions, surgical interventions, and endoscopic bariatric procedures [7]. Bariatric surgery (BS) is the most commonly performed procedure worldwide [10] and the most effective intervention for individuals with severe obesity (BMI greater than 40 kg/m^2^) [11], and includes a group of surgical procedures performed to facilitate weight loss, such as open or laparoscopic roux-en-Y gastric bypass, sleeve gastrectomy, and adjustable gastric banding. The most obvious and studied benefits of BS refer to physical issues, specifically weight loss and improvement of obesity-related physical comorbidities; however, between 10% and 25% of patients who undergo BS show suboptimal weight loss, and it is estimated that they regain approximately 10% of their weight during the first decade after the intervention [12]. Regarding the psychological benefits of BS, limited and inconclusive results have been found [13]. Some systematic reviews have reported improvements after BS, especially in depressive symptoms, but also limited only to the first months after the intervention, and they tend to reappear after the first two years [10].

Some studies have questioned whether previous psychopathology history could influence the results obtained by BS [2]. This topic is especially relevant because the percentage of psychopathology among people waiting for BS (between 20.9% and 55.5%) [12] is much higher than in the general population (between 12.53% and 13.87%) [14]. Specifically, the group of emotional disorders (ED), which includes anxiety and mood disorders, eating disorders, and related disorders ([15]; Supplementary Materials), are the most prevalent disorders among BS candidates: eating disorders (50%), mood disorders (31.5%), anxiety disorders (24%), and substance use related disorders (10%) [12]. It has been concluded that the presence of EDs among candidates for BS predicts worse results in the long term [11], furthermore, a meta-analysis states that the prevalence of suicide mortality is up to 1.8%, and the prevalence of suicide is up to 0.3% after bariatric surgery [16].

As we can observe, psychological evaluation and intervention play a fundamental role in the multidisciplinary work performed with these patients before and after BS although, until now, it has not received much attention [12]. Improvements in eating psychopathology (e.g., binge eating, emotional eating, body image dissatisfaction) have been reported from psychological interventions using psychoeducation, goal setting, self-monitoring, normalized eating, stimulus control, cognitive restructuring, and relapse prevention [11]. Cognitive–behavioral therapy (CBT) is the one that accumulates the most evidence of the improvement of eating behaviors (e.g., binge eating and emotional eating) and psychological functioning (e.g., quality of life, depression, and anxiety symptoms) [11]. Despite the good outcomes achieved, these CBT interventions have been developed to treat specific disorders (e.g., eating disorders or anxiety disorders), and this fact raises some limitations. First, clinicians’ great effort to specialize in a range of different interventions; second, the increased costs for health systems and clinicians in training, and as a consequence, the difficulties in dissemination and implementation of the CBT interventions [17]. Furthermore, if we consider that the most prevalent disorders among patients with obesity are EDs [12], there are additional limitations to specific CBT interventions. This is because in the case of these disorders, comorbidity is very high, and subclinical symptoms or unspecified disorders usually arise [18]. These comorbid conditions make it even more difficult to choose the best specific CBT treatment in each case [19].

To address all the limitations of the specific CBT treatments previously discussed, in recent years, different CBT interventions from a transdiagnostic approach have been developed and tested. In this sense, the Unified Protocol for the transdiagnostic treatment of EDs (UP) is a CBT emotion-based intervention designed to treat the etiological and maintenance mechanisms shared by all EDs [20]. This intervention focuses on a wide range of emotional psychopathology, considering comorbid disorders and subclinical or unspecified symptoms, reducing treatment times and costs, and improving response to treatment [17].

The UP is made up of eight treatment modules, five of which are considered core modules because they are focused on training different specific emotion-regulation skills [21]. Despite that the UP is a protocolized intervention, it is also flexible and versatile, allowing clinicians to use some of the modules or to change modules’ order to personalize the UP to their patients [22]. Its main objective is to enhance emotion-regulation strategies to all people presenting emotional dysregulation problems [15]. To date, the UP has shown a significant improvement in pre-treatment symptoms and has obtained effect sizes that are at least comparable to existing specific CBT interventions, in on-site and online formats [23]. Beyond the mood or anxiety disorders per se, the UP has been applied to different health problems, such as cancer [24], HIV [25], or irritable bowel syndrome [26]. Despite the positive data on the effectiveness of the UP for the treatment of EDs in different health conditions, we have found no studies about its clinical utility to improve anxiety and depressive symptoms or EDs in patients with obesity who are waiting for BS.

As mentioned, the UP can be applied in various formats, such as onsite or online (both individual and group). Regarding online interventions in mental health (e-Health), there is an important amount of evidence over the last 15 years informing that online treatments are effective to treat a wide range of mental health disorders and that they can be as effective as onsite treatments [27]. We also know that online interventions do not negatively affect the therapeutic relationship [28] and that the users generally show high levels of acceptance and satisfaction with this delivery format [29]. The use of Information and Communication Technologies (ICTs) reduces the burden on health professionals and users, facilitating data collection and accessibility to Treatment [30]. In fact, different studies have shown the need to develop technology-based interventions to increase accessibility to treatment for BS candidates because their obesity condition significantly affects their mobility, and that makes it difficult for them to attend weekly sessions on-site [31]. Another practical benefit of delivering online psychological interventions is related to the current situation caused by the Covid-19 pandemic because the online format (e.g., emails, videoconference, etc.) will allow phycologists to continue their interventions and/or the follow-up assessments in case of new mobility restrictions [32]. Finally, the online group format can offer additional advantages to the online format itself, as it facilitates social support among the participants in the therapy and also allows them to share experiences and learn from each other [33].

Therefore, the general objective of this study is to analyze the feasibility and clinical usefulness of the UP, applied in an online group format, in a mental health setting of the National Health System to candidates for BS who have at least one diagnosis of ED or emotional symptoms.

The specific objectives pursued are: to evaluate adherence to treatment and clinical improvement in the primary and secondary measures after applying the UP and to study its long term clinical usefulness until two years after the intervention. Thus, the main hypotheses proposed for this study are: (1) statistically significant differences (reliable change index; RCI) will be obtained between the scores obtained at the pre-treatment, baseline, and post-treatment on the primary and secondary measures; (2) the improvements obtained after the application of the UP will be maintained in the long term (follow-ups of up to two years); (3) participants in the pilot study will report high adherence rates and high satisfaction scores regarding the treatment delivery format and its components.

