## 2. Materials and Methods

This is a pilot study using a repeated single-case experimental design (multiple baseline design) to explore the feasibility and clinical usefulness of a transdiagnostic emotion-based online group intervention (UP) for BS candidates with EDs or subclinical anxious or depressive symptoms attended to in a public mental health service. We have chosen this design for three reasons: (1) the unit of intervention and unit of data analysis is an individual case, specifically a cluster of participants; (2) the case provides its own control for comparison purposes because a number of variables are measured before the intervention and compared with measures during and after the intervention and (3) the variable is repeatedly measured within and across different conditions or levels of the independent variable. Furthermore, and because our main objective is to answer the question “Is the Unified Protocol able to improve the emotional state of people waiting for BS?”, we chose a multiple baseline design to improve experimental control throughout replication, introducing the independent variable at different points in time. The fundamental idea of choosing this type of design is that each of the participants can be their own control group [34].

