### 2.5. Measures

The evaluation protocol will be administered online by Qualtrics survey [45] at five different moments: pre-treatment, baseline, treatment, post-treatment, and follow-ups every three months until two years after the intervention. Assessment instruments will include demographic characteristics (age, sex, education, marital status, and employment status), a diagnostic interview, and well-established questionnaires for both primary and secondary outcomes. Next, the primary and secondary outcomes that will be evaluated at the pre, post-treatment, and follow-up periods will be described, and later the specific measures that will be used for the baseline evaluation and during the treatment will be specified. Table 3 shows the distribution of the measures that will be administered during the study.

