#### 2.5.1. Primary Outcomes

Primary and secondary diagnosis according to the DSM-5 criteria will be evaluated with the International Neuropsychiatric Interview (MINI [50]). Subclinical symptoms of anxiety and depression will be evaluated through the Beck Depression Inventory-II (BDI-II [46,47]) and the Beck Anxiety Inventory (BAI [48,49]). The weight gain or loss of the participants will be evaluated through the Body Mass Index (BMI).

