**Contraindications**
Relative
- Clearly unfavorable family environment
- Personality disorder
- Psychogenic vomiting
- Hyperphagia in other psychological disorders or other eating disorders
- Mild intellectual disability
- Psychotic disorders without positive symptoms
- Any psychiatric illness that significantly hinders the good follow-up and completion of the guidelines and medical indications for this process and may worsen the patient’s state of health
Absolute
- Drug dependency
- Moderate or severe intellectual disability
- Psychotic disorder with positive symptoms
- Bulimia nervosa

**Table 2 ijerph-17-06155-t002:** Treatment content split by session.

Session Number	Content
Session 1	Setting Goals and Maintaining Motivation
Session 2	Understanding your Emotions: What is an Emotion?
Session 3	Understanding your Emotions: Following the ARC (Antecedent, Response, Consequence)
Session 4	Mindful Emotion Awareness—I
Session 5	Mindful Emotion Awareness—II
Session 6	Cognitive Flexibility—I
Session 7	Cognitive Flexibility—II
Session 8	Countering Emotional Behaviors
Session 9	Understanding and Confronting Physical Sensations
Session 10	Putting it into Practice: Emotion Exposures—I
Session 11	Putting it into Practice: Emotion Exposures—II
Session 12	Recognizing Accomplishments and Looking to the Future

**Table 3 ijerph-17-06155-t003:** Distribution of the variables administered throughout the intervention.

Measures	Pre-Treatment	Baseline	Treatment	Post-Treatment	Follow-Ups ^1^
Demographic characteristics	X				
MINI	X			X	X
BDI-II	X			X	X
BAI	X			X	X
BMI	X	X	X	X	X
PANAS	X			X	X
NEO-FFI	X			X	X
QLI	X			X	X
EuroQol	X			X	X
MI	X			X	X
DERS	X			X	X
BEAQ	X			X	X
PHLMS	X			X	X
ERQ	X			X	X
Surgical Complications	X				
BITE	X			X	X
BSQ	X			X	X
EES	X			X	X
OASIS			X		
ODSIS			X		
OESIS			X		
PESIS			X		
STQ				X	X
Baseline assessment battery ^2^		X			
Assessment battery during treatment ^3^			X		

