**Individual Results:**
- To obtains statistically significant differences (Reliable Change Index; RCI) between the scores obtained at the pre-treatment, baseline, and post-treatment on the primary and secondary measures.
- A maintaining of improvements obtained after the application of the UP in the long term (follow-ups of up to two years), with statistically significant differences (Reliable Change Index; RCI) between the scores obtained at the pre-treatment/post-treatment and follow-ups on the primary and secondary measures.

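### Hypothesis 1 promises a pre-treatment, baseline and post-treatment comparison on the primary and secondary measures, but MINI, BDI-II, BAI and the full secondary questionnaires are never given in the baseline phase

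*Protocol article*

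**What the plan says.** The last paragraph of section 1 (Introduction) states Hypothesis 1: statistically significant differences by RCI "will be obtained between the scores obtained at the pre-treatment, baseline, and post-treatment on the primary and secondary measures". Table 4, under individual results, repeats the expectation of RCI differences "between the scores obtained at the pre-treatment, baseline, and post-treatment on the primary and secondary measures".

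Section 2.5.1 names four primary outcomes. The first is diagnosis: "Primary and secondary diagnosis according to the DSM-5 criteria will be evaluated with the International Neuropsychiatric Interview" (MINI). The next two are symptom scales: "Subclinical symptoms of anxiety and depression will be evaluated through the Beck Depression Inventory-II" and the Beck Anxiety Inventory. The fourth is BMI.

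On timing, section 2.5 announces that "the primary and secondary outcomes that will be evaluated at the pre, post-treatment, and follow-up periods will be described", and that the measures used at baseline and during treatment are set out separately afterwards. Table 3 ("Distribution of the variables administered throughout the intervention") agrees. MINI, BDI-II and BAI are marked at pre-treatment, post-treatment and follow-ups, and are blank at baseline and during treatment. BMI is marked at all five moments. Section 2.5.2 adds that weight is checked monthly.

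Section 2 (Materials and Methods) justifies the design partly because "the case provides its own control for comparison purposes" and because the variable is measured repeatedly within and across conditions. It adds that, like a randomised trial, a multiple baseline design can show that a change results from the intervention.

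**The concern.** A multiple baseline design takes its control from a variable that is measured repeatedly before treatment, with treatment starting at staggered times. If the variable changes when treatment starts and not before, the change can be credited to treatment. An outcome not measured in the baseline phase has no such control, whatever baseline length its participants were randomised to.

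Hypothesis 1 is worded as if the primary and secondary measures had a baseline score, and the schedule gives one only to BMI. Two things are at stake. The baseline part of a stated main hypothesis cannot be tested on most of the measures it names. And a reader of the results could credit a fall in BDI-II or BAI to treatment on the strength of a design that was not applied to those scales.

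**Working it through.** No sample-size or power formula decides this point. The check sets the hypothesis beside the schedule.

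**1. Is baseline a separate moment from pre-treatment?** Yes. Hypothesis 1, section 2, section 2.5 and Table 3 all list the two separately, and section 2 places the pre-treatment assessment before the baseline starts.

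**2. What does Table 3 collect, and when?**

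| Measure | Pre | Baseline | Treatment | Post | Follow-ups |
|---|---|---|---|---|---|
| MINI, BDI-II, BAI (primary) | yes | no | no | yes | yes |
| BMI (primary) | yes | yes | yes | yes | yes |
| 12 secondary questionnaires | yes | no | no | yes | yes |
| Baseline and treatment batteries (single items) | no | yes | yes | no | no |

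The 12 questionnaires are PANAS, NEO-FFI, QLI, EuroQol, MI, DERS, BEAQ, PHLMS, ERQ, BITE, BSQ and EES. Surgical complications (pre-treatment only) and the STQ (post-treatment and follow-ups only) are left out, because neither is marked at both pre and post.

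Instruments marked at both pre and post: 3 + 1 + 12 = 16. With a baseline mark: 1 (BMI). Without: 16 − 1 = 15, including three of the four primary outcomes.

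**3. Do the daily items fill the gap?** Section 2.5.3 lists items on specific emotions (sadness and anxiety among them), and items drawn from DERS, ERQ, PHLMS, BEAQ, EES and BSQ. None comes from MINI, BDI-II or BAI. Six of the 12 secondary questionnaires thus have a daily proxy; PANAS, NEO-FFI, QLI, EuroQol, MI and BITE have no item drawn from them. A single item cannot be entered in an RCI with a full-scale score. Table 3 marks the batteries at baseline and treatment only, so these items allow a baseline-versus-treatment comparison, not the three-point one in Hypothesis 1.

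**4. What does BMI gain?** The baseline lasts at most 15 days and weight is checked monthly, so there is about one reading in the phase. That allows a pre/baseline/post comparison but no baseline trend. Section 2 itself cites a minimum of five data points per phase.

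**5. What interval do MINI, BDI-II and BAI cover?** Twelve weekly sessions are 12 × 7 = 84 days. Adding the baseline and assuming no gaps gives 8 + 84 = 92, 12 + 84 = 96 and 15 + 84 = 99 days from pre to post. The stagger is 15 − 8 = 7 days, or 7/99 = 7% of the longest interval, and nothing is scored on these instruments when treatment starts.

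**6. What is mixed into that pre-post change?** Treatment, the passage of time, the effect of being assessed, and possibly regression to the mean. Section 2 concedes that assessment may itself be therapeutic and puts the pre-treatment assessment before the baseline for that reason. To separate that effect on BDI-II and BAI, the same scales would have to be given again before treatment, and they are not.

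**The case against.** The strongest reply is that the own-control logic is applied, only through other instruments. Sadness and anxiety are rated daily at baseline and weekly in treatment, six secondary scales have an item chosen for its factor loading, and section 2.6 plans a visual analysis of these items by phase and module. This stands: the emotional state of participants is followed across phases. It does not rescue the wording of Hypothesis 1, which speaks of the primary and secondary measures and of RCI.

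A second reply is that Hypothesis 1 is one of three main hypotheses, that its pre-to-post part is fully testable, and that the study is a pilot whose Discussion calls for caution and further trials. This also stands and limits the severity. The general caution does not disclose this particular gap, however.

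A reader might infer that all primary outcomes lack a baseline score, or that Hypothesis 1 is untestable altogether. The article supports neither: BMI is marked at baseline, and pre versus post can be tested for every scale.

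A reader might also want to size the regression to the mean, since section 2.3 admits participants on moderate BDI-II and/or BAI scores. With selection 1 SD above the candidate mean and a test-retest correlation of 0.7 to 0.9, (1 − r) × 1 SD gives 0.3 to 0.1 SD. Neither input is in the article. Entry is also possible on a MINI diagnosis alone, and section 2.2 places the pre-treatment evaluation after eligibility and consent. If the scales are repeated there, much of the regression could precede the pre-treatment score. The amount could be near zero, and the point does not rest on it.

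**Conclusion.** The contradiction holds. Hypothesis 1 and Table 4 promise baseline comparisons on measures that section 2.5 and Table 3 do not collect in the baseline phase: 15 of the 16 instruments given before and after treatment, including MINI, BDI-II and BAI. For those three primary outcomes the randomised stagger gives no own-control comparison, and what can be reported is an uncontrolled pre-post change over about 92 to 99 days, assuming no gaps. BMI escapes the contradiction but gains little, with about one baseline reading. The bias in the pre-post change cannot be sized from the article. The counts rest only on Table 3 and the list of items in section 2.5.3. This should be fixed, because it changes what may be concluded about the primary symptom measures. It does not undermine the feasibility aims or the phase analysis of the daily items.

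**What to change.** Reword Hypothesis 1 and the matching entry in Table 4 so that baseline is claimed only for measures collected in that phase: BMI, and the daily items as a baseline-versus-treatment comparison. Describe MINI, BDI-II, BAI and the full secondary scales as uncontrolled pre-post comparisons, and state that the causal claim made for the design in section 2 is not drawn from them. This costs a few sentences.

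A cheap optional addition is to repeat BDI-II and BAI online once, on the last baseline day (day 8, 12 or 15), and to report the change from pre to end of baseline next to the change from end of baseline to post. Participants are already completing online items on that day, so the extra burden is slight. It would be only partial control: one reading after 8 to 15 days, set against about 12 weeks of treatment and below the five points per phase that the protocol cites. If it is adopted, Table 3 needs a baseline mark for both scales, and Hypothesis 1 may then name them.
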